## **4. TRIAL DESIGN**

### **4.1 Type of study, description of study design**

The trial is planned as a multicenter, 1:1 randomised, parallel group, comparative, open study. The study may be expanded to other Swiss or a foreign state centers. The patients included into the study will receive standard immunosuppression therapy consisting of Tacrolimus / MMF / steroids / IVIG / ATG-Fresenius S bolus therapy in one arm and in the other arm Tacrolimus / MMF / steroids / IVIG / Thymoglobulin, respectively.

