### **4.2 Randomisation**

To avoid bias due to patient selection the patients will be assigned to the investigational treatments by randomization. Patients will be assigned a consecutive number in the order in which they enter the trial. The assignment of consecutive numbers will be done within each participating center. Each center will receive a set of sealed random code envelopes which will be labelled with an identification of the trial and a unique treatment number and will contain a note with the identity of treatment assigned to this number. After a patient has been included into the trial, his/her eligibility has been confirmed and he/she is ready to receive the investigational treatment, the investigator will break the seal of the envelope bearing the lowest available number and will administer the treatment corresponding to the included note. The random code envelope must not be opened before the eligibility of a patient has been finally determined and he/she is ready for treatment. Details will be given to the participating investigators.

Patient population:

Recipients, who are at least 18 years or older and have a high immunological risk defined by:

The presence of at least one donor-specific antibody (class I and/or II) detected and specified by flow-technology (FlowPRA and single antigen Flow-beads), which are

- For class I below the threshold of detection of a current CDC T-cell- and B-cell cross-match
- For class II below the threshold of detection of a current CDC B-cell cross-match

Screening failure (Drop-out)

Patients can be replaced by new patients before being randomised. After the randomisation has been performed a replacement of a drop-out is not allowed. Every patient that has been randomised and included in the study will be considered at least in the safety analysis.

To ensure an unbiased assessment of AEs a blind cross-over evaluation of all events will be done. The physicians in Basel will assess the causal relationship of AEs to the investigational treatment in patients treated in Zürich and *vice versa*. The appraisal will be done provided by the treatment e.g. either with ATG-Fresenius S or Thymoglobulin but without knowing.

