**→ Primary endpoint is reached when 1 event of 1 to 4 is positive.**

Anaphylaxis is a clinical diagnosis consisting of following possible symptoms: elevated temperature, generalized exanthema (flush), edema, dyspnea, stridor and hypotension.

Serum sickness is a clinical diagnosis consisting of following possible symptoms occurring after 6 to 14 days and lasting for 1 to 5 days: sudden fever, generalized exanthema, arthritis, meningitis, nephritis, enteritis and polyserositis.

These symptoms will be evaluated as attributable adverse events if a causal relationship with the investigational treatment cannot be excluded (i. e., causality assessment "probable", "possible" or "unlikely"; see section 7.3 G for details).

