## 6. TREATMENT OF SUBJECTS

### 6.1 Administration route, single dose, dosage, treatment period, follow-up for subjects

All patients included will provide written informed consent to participate in the trial.

Blood parameters will be determined before study drug administration which will be used as baseline values.

In women of childbearing age a pregnancy test will be performed before inclusion.

Patients qualified for the trial will be randomised to one or the other treatment.

The treatments will be administered as open therapies. A central venous catheter will be placed and kept open using a normal saline or glucose infusion drip or a fistula. This line will be used to administer test treatments.

Intravenous methylprednisolone sodium succinate (see table "therapy scheme I and II") should be given 1 hour before administering the test drugs.

Patients randomised to receive a bolus therapy with ATG-Fresenius S will be treated i.v. with a 9 mg/kg bw bolus of ATG-Fresenius S, which is diluted in 100-500 ml physiological saline. The infusion has to be applied completely before reperfusion (infusion time at least 1 hour). After this first infusion the patients receive 3 mg/kg bw/d for 4 days given over 4 hours.

Patients randomized to receive Thymoglobulin will be treated i.v. with 1.5 mg/kg bw of Thymoglobulin, which is diluted in 100-500 ml physiological saline. The infusion has to be completed before reperfusion (infusion time at least 1 hour). After this first infusion the patients receive 1.5 mg/kg bw/d for 3 days given over 4 hours.

The patients will be observed closely for the first 2 hours of treatment.

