### **7.2 Methods and timing for assessing, recording, and analysing of safety parameters**

Adverse events, reported by the patient and/or observed by study personnel, will be summarized for each treatment group. Laboratory data will be compared to the corresponding normal ranges. Physiopathologically relevant high or low parameters will be summarized for each treatment group. Per protocol all AE documentation is performed continuously.

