**5 = assessment impossible**

- the available data are insufficient for any reasonable assessment with respect to a causal connection

In this open-label trial the causality assessments of all adverse events will be provided by blind raters. The rater will receive all information available for a particular adverse event, including predisposing factors from the patients' history, concomitant medication and diseases, but he/she will be unaware of the investigational treatment actually received. For each adverse event two different causality assessments will be obtained: (a) assuming that the patient has received ATG and (b) assuming that he/she has received Thymoglobulin. During data analysis only the assessment corresponding to the treatment actually received will be used.

All cases where 1, 2 or 3 applies will be evaluated as attributable adverse events / ADRs.

All adverse events, i. e. also the already known ADRs, must be documented and serious adverse events also be registered. There is also an obligation to registration if a causal relationship is not supposed resp. not evident. The following items must be registered:

- Precise trial subject data;
- precise description of the AE;
- precise recording of the time of the AE in relation to the course of therapy;
- intensity of the AE;
- results of diagnostic and therapeutic measures,
- where applicable, rechallenge and/or dechallenge data;
- course and outcome of the AE;
- severity of the AE, including medical assessment;
- all other important data that may be of relevance for assessment of a possible relationship between the AE and the administration of the investigational medical substance.

Data are documented and registered on the form "adverse events" or „serious adverse events“ (see enclosure 4), whereby the needed additional information can be supplied without a specific form.

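### The blinded cross-centre review rates causality only; nothing provides blinded confirmation that a reaction is anaphylaxis, serum sickness or an item 3 event

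*Protocol*

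**What the plan says.** **Open treatment.** Section 4.1: "The trial is planned as a multicenter, 1:1 randomised, parallel group, comparative, open study". Section 6.1: "The treatments will be administered as open therapies".

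**The safeguard.** Section 4.2 states its purpose broadly: "To ensure an unbiased assessment of AEs a blind cross-over evaluation of all events will be done". The task then described is causal relationship: "The physicians in Basel will assess the causal relationship of AEs to the investigational treatment in patients treated in Zürich", and vice versa. Section 7.3 g matches this: "In this open-label trial the causality assessments of all adverse events will be provided by blind raters". The rater receives the available information on the event without the treatment identity and rates causality twice, once under each assumed drug. The analysis uses the rating for the drug actually given.

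**How events arise.** Section 7.2: "Adverse events, reported by the patient and/or observed by study personnel, will be summarized for each treatment group". Section 7.1 adds that symptoms are asked about actively.

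**What makes an event.** Section 4.3.1 gives four items, any one of which reaches the primary endpoint.
- Item 1: "Anaphylaxis is a clinical diagnosis consisting of following possible symptoms: elevated temperature, generalized exanthema (flush), edema, dyspnea, stridor and hypotension".
- Item 2, serum sickness, is also a clinical diagnosis from a list of possible symptoms, with onset after 6 to 14 days and a duration of 1 to 5 days.
- Item 3 requires two of four symptoms, with fever set at above 38°.
- Item 4 covers haematological findings with numerical limits, severe infection defined by care needed, malignancy, and safety withdrawals.

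**Which events count.** Sections 4.3.1 and 7.3 g count ratings of probable, possible and unlikely as attributable. Section 9 analyses each listed reaction separately, at 20 patients per arm.

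**The concern.** An event enters the item 1 to 3 analyses in two steps: someone decides that an episode meets an item, and someone decides whether the drug could have caused it. The protocol blinds the second step. The first is where judgement is widest, at least for anaphylaxis and serum sickness, and it is not covered.

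The direction of any bias is foreseeable. Section 3 expects the safety profile of ATG-Fresenius S may be superior, section 2.5.2 presents it as the milder product, and safety is the primary outcome. A physician who knows the drug could, without intent, label borderline reactions differently in the two arms. Differences in items 1 to 3 would then partly reflect labelling, and a reader of section 4.2 would believe this had been prevented.

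**Working it through.** **1. Scope of the blinded step.** The protocol states no figure on this point, so the first check is textual.

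| Question about an episode | Blinded rater? | Where |
|---|---|---|
| Is it causally related? | Yes | 4.2, 7.3 g |
| Is it anaphylaxis (item 1)? | Not provided | 4.3.1 |
| Is it serum sickness (item 2)? | Not provided | 4.3.1 |
| Does it meet item 3? | Not provided | 4.3.1 |

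**2. How much the definitions fix.**

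| Item | Minimum symptoms | Timing |
|---|---|---|
| 1 Anaphylaxis | None stated; six possible symptoms | None stated |
| 2 Serum sickness | None stated; seven possible symptoms | Onset 6–14 days, duration 1–5 days |
| 3 Symptom pair | Two of four, fever above 38° | No same-episode rule |

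Section 4.3.1 counts events at any time during treatment and follow-up. Read literally, two item 3 symptoms from unrelated episodes would qualify.

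**3. What blinded causality can remove.** Of the five categories, three count as attributable. An event drops out only if rated no relationship or assessment impossible. Under 7.3 g, the former is described by the absence of a reasonable temporal sequence and by an obvious other cause. A reaction soon after an infusion will seldom lack a temporal sequence, so the filter is likely to be weak for items 1 and 3. How weak cannot be computed from the protocol.

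**4. Item level versus composite.** Section 9 analyses each listed reaction separately, so a changed label changes an item count directly. The composite needs any one of four items. A doubtful label changes it only in a patient positive on nothing else. Moving an episode between items 1, 2 and 3 does not change it.

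**5. Size, as an illustration.** From the protocol: n = 20 per arm, two-sided Fisher's exact test, indicator p ≤ 0.15 (section 9). Assumed, because the protocol gives no rates: a true rate π for one item in both arms, and a spurious rise δ in one arm from unblinded labelling.

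Pr(flag) = Σₐ Σ_b Bin(a; 20, π) × Bin(b; 20, π + δ) × 1[Fisher p(a, b) ≤ 0.15]

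| π | δ = 0 | δ = 10 points | δ = 20 points |
|---|---|---|---|
| 10% | 4.0% | 15.4% | 40.5% |
| 20% | 6.5% | 14.0% | 33.1% |
| 30% | 6.9% | 13.3% | 31.7% |
| 40% | 7.6% | 14.0% | 31.9% |
| 50% | 8.1% | 14.0% | 31.7% |

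Ten points is 0.10 × 20 = 2 patients. From a 30% base, two extra labels on average multiply the chance of a flag by 13.3 / 6.9 = 1.9, and four by 31.7 / 6.9 = 4.6.

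**6. Sensitivity to the indicator.** Section 9 lists four indicators joined by a conjunction. Requiring p ≤ 0.15 together with both 95% intervals excluding no effect (Newcombe interval for the difference, log-scale interval for the ratio, the risk-ratio size condition left out), the chances at π = 30% are 2.4%, 6.8% and 20.6%. The level falls, but the relative rise is larger: 6.8 / 2.4 = 2.8 and 20.6 / 2.4 = 8.6.

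**The case against.** **The definitions are not empty.** Item 3 has a count and a fever limit, and serum sickness has onset and duration limits. This stands. A reader might infer that all of items 1 to 3 lack minimum criteria; that is true only of anaphylaxis and of the symptom count for serum sickness. Nor does the protocol say that one sign, such as raised temperature, suffices for anaphylaxis: it asks for a clinical diagnosis and leaves the threshold unstated.

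**Nobody is named as classifier.** This also stands. That unblinded local staff decide is inferred from the open design and section 7.2. The opening sentence in 4.2 refers to evaluating all events, and the event forms and case report form are not shown. However, 4.2 and 7.3 g both specify causality and nothing else.

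**Much of the endpoint needs no label.** Item 4 rests largely on laboratory limits and hospital care, and item 3 can be derived from recorded symptoms. A reader might infer that unblinded diagnosis decides the primary endpoint as a whole, or that fever and rash appearing under several items distorts it. The any-of-four rule does not support either. The exposure lies mainly in the item-level analyses.

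**This is a descriptive pilot, and the bias sizes are invented.** Both are fair. No confirmatory claim is at stake, and the percentages show sensitivity only. But the item-level safety comparisons are the product of this pilot, and the protocol itself undertakes to assess events without bias.

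**Blinded raters work from what unblinded staff wrote.** True. Blinded classification reduces the bias but cannot eliminate it. Active questioning about symptoms helps in part.

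**Conclusion.** The point holds in a limited form. The blinded review is described as securing unbiased assessment of all events, but it covers causality only. The protocol provides no blinded confirmation that a reaction is anaphylaxis or serum sickness, sets no minimum symptom set for either, and has no same-episode rule for item 3. Because unlikely counts as attributable, the blinded rating is expected to filter few events, which leaves the separate analyses of items 1 to 3 open to unblinded classification bias. The composite is exposed only in patients positive on no other item.

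The actual size is unknown. For base rates of 10% to 50%, a spurious 10-point shift gives a 13% to 15% chance of meeting p ≤ 0.15, against 4% to 8% without bias. That rests on assumed rates, on an assumed shift and on one of the four indicators. The conclusion also assumes that classification is done locally with knowledge of the drug. The documents do not show that such bias will occur, only that the stated safeguard does not reach this step.

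**What to change.** Extend the existing raters' task in sections 4.2 and 7.3 g.

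1. Before rating causality, and from the same packet masked for drug name and dosing pattern, the rater records which of items 1 to 3 the documented signs and symptoms meet. More than one item is allowed, since section 4.3.1 wants events both individually and in combination. One classification per event is enough, because it does not depend on the assumed drug.
2. In section 4.3.1, pre-specify a minimum symptom set for anaphylaxis and for serum sickness, keeping the latter's time limits, and state whether item 3 symptoms must occur in the same episode. The investigators should set this content before the first event is rated.
3. In section 9, use the blinded classification for the primary analyses of items 1 to 3 and the composite, and repeat them with the local diagnosis as a sensitivity analysis.
4. Reword the aim in 4.2 to say that classification and causality are assessed blind, while elicitation and recording remain open.

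The cost is one added entry on the rating form, a short criteria list and slightly more rater time. The raters and source material stay the same, and neither patient care nor sample size changes. Bias in which symptoms local staff elicit and record would remain.

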### 4.3 Primary and secondary endpoints

The main target variables are safety parameters (side effects, infections, lymphoma, and malignancies). Secondary endpoints are efficacy parameters (rejections, patient/graft survival, and lymphocyte depletion).

#### 4.3.1 Primary endpoints

The main target variables are safety parameters. Variables to be assessed are incidences of selected adverse events. The primary outcome measure of the trial is the incidence of the following signs and symptoms (individually and in combination) at any time during randomized treatment and follow-up:

1. Anaphylaxis
2. Serum sickness
3. Two of the following symptoms: Fever  $>38^{\circ}$ , chills, nausea/vomiting or erythema
4. One of the following findings:
  - Hematological side effects (leucopenia ( $<3000$ ), thrombocytopenia ( $<50'000$ ), hyporegenerative anemia (hemoglobin  $< 100\text{g/l}$  plus non-elevated reticulocytes or erythropoietin substitution)
  - Severe infectious complications defined by prolonged hospital stay, needing ICU or re-hospitalization.
  - Lymphoma, post-transplant lymphoproliferative disease (PTLD), malignancy
  - Number of patients withdrawn due to adverse events or for other safety-related reasons

**→ Primary endpoint is reached when 1 event of 1 to 4 is positive.**

Anaphylaxis is a clinical diagnosis consisting of following possible symptoms: elevated temperature, generalized exanthema (flush), edema, dyspnea, stridor and hypotension.

Serum sickness is a clinical diagnosis consisting of following possible symptoms occurring after 6 to 14 days and lasting for 1 to 5 days: sudden fever, generalized exanthema, arthritis, meningitis, nephritis, enteritis and polyserositis.

These symptoms will be evaluated as attributable adverse events if a causal relationship with the investigational treatment cannot be excluded (i. e., causality assessment "probable", "possible" or "unlikely"; see section 7.3 G for details).

#### **4.3.2 Secondary endpoints**

- Incidence of acute rejection episodes and type (cellular or humoral) of rejection (according to Banff)
  - Total number and type of anti-rejection treatments
- Graft function
  - Serum creatinine at day 1, 7, 14, and month 1, 3, 6, 12
  - Proteinuria month 1, 3, 6 and 12
- Graft and patient survival

#### **4.4 Time schedule**

The recruitment will start in November 2008. The enrolment will continue approximately 24 months until the desired patient number is reached, followed by a 12- month observation period.

Duration of treatment for:

ATG-Fresenius S: 5 days (per protocol)

Thymoglobulin: 4 days (per protocol)

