### 6.2 Transplant monitoring

#### Standard monitoring:

- The patients will be followed by the routine clinical, biochemical and imaging parameters.
- Blood pressure, heart rate, temperature and urine output will be recorded daily during hospitalisation.
- Standard blood work as routinely done includes:
  - Complete blood count (including hemogram, leukocytes, reticulocytes and platelet count).
  - Complete blood chemistry (including serum creatinine, blood urea nitrogen (BUN), sodium, potassium, calcium, phosphate, uric acid, total protein, albumin, bilirubin, SGOT (AST), SGPT (ALT), LDH, gamma-GT, alkaline phosphatase, glucose, cholesterol and HbA1c).
- Standard blood work will be performed at each visit and at least at days 0, 1, 7, 14 and at months 1, 3, 6, 12 and 24.

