## 9. STATISTICS

In this pilot study all statistical analyses will be descriptive and p-values will be interpreted accordingly. Confidence intervals will be provided to assist the interpretation of the observed effects.

The primary analysis of safety will assess the incidence of adverse drug reactions (ADRs) attributable to the investigational treatments according to the causality assessment detailed in Section 7.3, paragraph G. A separate analysis will be performed for each of the ADRs listed in Section 4.3.1 as well as for a summary of all ADRs not included in this compilation.

For comparison between ATG and Thymoglobulin the risk ratio (ratio of proportions of patients reporting a particular ADR at least once under trial drug and reference treatment) and the risk difference (difference between proportions) will be determined, including their 95% confidence intervals determined according to the method described by Newcomb (25). For comparisons between the AE rates under both treatments, descriptive two-sided p-values will be determined with Fisher's exact test. In a working definition, the following findings will be considered to be indicators of a potentially meaningful treatment group difference regarding ADR incidence:

- two-sided p-value  $\leq 0.15$  for the comparison of AE rates,
- risk ratio  $\geq 0.5$  or  $\leq 2.0$ ,
- 95% confidence interval for a risk ratio which excludes the value 1.0, and
- 95% confidence interval for a risk difference which excludes the value 0.0.

All analyses of safety will be performed primarily in the safety data set which includes all patients who have received the investigational treatment at least once. To assess potential bias introduced by premature withdrawal from the trial a sensitivity analysis will be performed in a subset which includes all patients who complete the follow-up period as scheduled (but independently of the presence or absence of protocol violations).

For the analysis of treatment efficacy actuarial life tables will be computed for the following parameters: graft survival, patient survival, time to first rejection episode. All life tables will be based on a period of observation of 24 months.

---

 Relevance criteria derived from (26).

In addition, inferential statistics will be computed for the following parameters:

- Time to 1st and 2nd rejection (Mann-Whitney U-Test).
- Incidence of rejection episodes (Chi-square statistic).

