- Number of rejections per patient (Mann-Whitney U-Test).
- Duration of rejection episodes (t-test).
- 12, and 24-months graft survival rate (Chi-square statistic).
- 12 and 24-months patient survival rate (Chi-square statistic).
- Number of prednisone pulses within 12 and 24 months (Mann-Whitney U-Test).
- Rejection reversal rate (Chi-square statistic).

The analysis of efficacy will be based on the full analysis set (FAS) which includes all patients who were randomized and treated and for whom any post-treatment efficacy data are available.

After completion of the 24-months follow-up period the final biometrical analysis will be performed.

Furthermore, all patient data recorded in the trial database will be tabulated by treatment group using methods of descriptive data analysis, with specification of summary statistics applicable to their levels of measurement.

Sample size estimation:

In this pilot study the determination of the sample sized is based primarily on feasibility rather than on statistical reasons. A total of 40 (Zürich 20, Basel 20) randomised and treated patients (20 in each treatment group) will be included.

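### Section 4.4 plans 12 months of observation after enrolment, while Sections 6.2 and 9 need 24 months; the follow-up length, and with it the primary endpoint window, must be stated once

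*Protocol*

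**What the plan says.** Section 4.4 gives the calendar. "The enrolment will continue approximately 24 months", and it goes on "until the desired patient number is reached, followed by a 12- month observation period".

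Section 9 uses a different length. For graft survival, patient survival and time to first rejection: "All life tables will be based on a period of observation of 24 months". Two chi-square comparisons are planned at two time points each: "12, and 24-months graft survival rate (Chi-square statistic" and "12 and 24-months patient survival rate (Chi-square statistic". Prednisone pulses are also to be counted over both 12 and 24 months and compared by Mann-Whitney test. On timing: "After completion of the 24-months follow-up period the final biometrical analysis will be performed".

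Section 6.2 requires standard blood work "at least at days 0, 1, 7, 14 and at months 1, 3, 6, 12 and 24", and under optional monitoring it lists lymphocyte subsets out to month 24. In Section 4.3.2 the two graft-function measures stop at month 12 (creatinine, and "Proteinuria month 1, 3, 6 and 12"). Rejection, anti-rejection treatment, and graft and patient survival carry no time point there.

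The primary endpoint in Section 4.3.1 counts events over the whole of treatment and follow-up, without a length in months.

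**The concern.** Sections 4.4 and 9 both speak of a period of observation and give it different lengths. This is not a detail left to a later analysis plan, because the protocol states both figures and they disagree.

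Two things are at stake. First, the planned 24-month comparisons need patients observed to month 24, and 4.4 taken as written does not provide that for the whole cohort. Second, several rules depend on the same number:

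- the primary endpoint window (4.3.1);
- the sensitivity subset of patients who complete scheduled follow-up (9);
- how long patients who stop treatment early are followed (4.5);
- how long adverse event outcomes are recorded (7.4).

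The primary analysis compares simple proportions of patients with at least one event, using a risk ratio, a risk difference and Fisher's exact test. No adjustment for exposure time is stated. The incidence of late components (malignancy, post-transplant lymphoproliferative disease, severe infection) therefore depends on how long patients are watched. Two centres could each follow the protocol and stop at different times, and late follow-up may not be recoverable once patients have left.

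**Working it through.** **Inputs from the protocol.** 40 patients, 20 per arm (20 + 20 = 40, which agrees with Section 9; the size rests on feasibility, so there is no power figure to reproduce). Enrolment about 24 months and observation 12 months (4.4). Analysis horizon 24 months (9).

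**Assumptions.** Uniform accrual over the 24 months, no dropout or death. The accrual assumption is varied below.

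**Calendar implied by each section.** Section 4.4: 24 + 12 = 36 months. Section 9, with every patient observed to month 24: 24 + 24 = 48 months.

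**Who reaches month 24.** For a patient entering at month e (0 to 24) with the trial closing at month C, potential follow-up is C − e.

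| Reading | Follow-up per patient | Reach month 24 |
|---|---|---|
| (a) 4.4 means 12 months for each patient | 12 months | 0 of 40 |
| (b) 4.4 means a common close, C = 36 | 36 − 24 = 12 to 36 − 0 = 36 months, mean 24 | those with e ≤ 12: 12/24 = 50%, about 20 of 40 |
| (c) Close 24 months after the last enrolment, C = 48 | at least 48 − 24 = 24 months | 40 of 40 |

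Under (b) the count is 40 × the share enrolled in the first year: 40 × 0.30 = 12 and 40 × 0.70 = 28, so 12 to 28 for shares of 30% to 70%.

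**What each reading leaves of Section 9.**

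- Under (a) there are no data beyond month 12, so no 24-month result exists.
- Under (b) the actuarial tables can run to month 24 with censoring. The chi-square comparisons of 24-month rates and the Mann-Whitney comparison of 24-month pulse counts need each patient's status or count at month 24, which is available for only part of the cohort. A final analysis placed after a completed 24-month follow-up would also not be true of later entrants.
- Under (c) everything in Section 9 can be done.
- The 12-month survival rates and pulse counts can be produced under all three.

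**Exposure behind the primary endpoint.** A fixed 12-month window gives 40 × 12 = 480 patient-months, and a fixed 24-month window gives 40 × 24 = 960. Reading (b) averages 24 months per patient, but with a threefold spread (12 to 36). As an illustration only, under an assumed constant hazard a 12-month incidence p becomes 1 − (1 − p)² at 24 months: 10% becomes 19%, and 20% becomes 1 − 0.8² = 36%. A late component could thus nearly double with the choice of window.

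**The case against.** The other side has several good points.

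- **The 24-month results are not all lost.** A reader might infer that none of the planned results can be produced. That holds only for the 24-month results, and only if 4.4 means 12 months per patient. The sentence stands under a time-schedule heading and can be read as a calendar close, in which case censored life tables remain valid and about half the cohort reaches month 24. The 12-month results are safe throughout. This stands.
- **Month-24 data collection is foreseen.** Sections 6.2 and 9 agree with each other, so 4.4 looks like the outlying sentence. This also stands. It makes the correction easier but does not remove the contradiction.
- **The secondary endpoints do not all stop at month 12.** Only creatinine and proteinuria do, and Section 9 names no 24-month analysis of either. Their month-12 limit is therefore no conflict in itself.
- **The primary window is not undefined.** It is defined in words as treatment plus follow-up; only its length is ambiguous. Anaphylaxis and serum sickness arise close to the 4 to 5 days of treatment and hardly depend on 12 versus 24 months.
- **Unequal exposure does not favour one arm.** The arms are randomised 1:1 and concurrently, so staggered follow-up would affect both alike on average. What suffers is the meaning of the absolute incidence.
- **This is a small descriptive pilot.** That limits the consequences, but a descriptive incidence still needs a stated period.

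**Conclusion.** The contradiction is real, and no section resolves it. Following 4.4 as written leaves the 24-month rate comparisons and pulse counts with no patients (12 months each) or with an incomplete cohort (common close). The incomplete cohort is about 20 of 40 under uniform accrual, and 12 to 28 if 30% to 70% enrol in the first year. These counts rest on the assumed accrual pattern and ignore dropout and death, which would lower them.

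The length of the primary window and the membership of the completer subset are ambiguous for the same reason. That matters for malignancy, lymphoproliferative disease and severe infection, and for reading any absolute incidence. The documents do not support the stronger readings that the whole set of planned results is unobtainable, that the primary window is missing, or that the comparison between arms is systematically biased.

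**What to change.** Align 4.4 with Sections 6.2 and 9: state that each patient is followed for 24 months and that the study ends 24 months after the last transplantation. The price is 12 more months of trial duration, about 48 in total instead of 36. The month-24 blood work is already in 6.2.

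If 12 months is what is meant, remove the 24-month life tables, rates and pulse counts and the month-24 measurements, and move the final analysis to the end of the 12-month follow-up.

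In either case, name one follow-up length, the same for every patient, as the window for the primary endpoint, and let the completer subset and Sections 4.5 and 7.4 refer to it. This is a short amendment.

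Two further changes are optional: adding month 24 to the creatinine and proteinuria endpoints, and limiting the primary endpoint to month 12 with later events reported separately. The second is debatable, because it would take later malignancies out of the primary endpoint, and Section 2.2.4 presents the trial as a response to a call for long-term follow-up.
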